## Abstract

**Background:**

Chronic tinnitus is a frequent condition, which can have enormous impact on patient's life and which is very difficult to treat. Accumulating data indicate that chronic tinnitus is related to dysfunctional neuronal activity in the central nervous system. Repetitive transcranial magnetic stimulation (rTMS) is a non-invasive method which allows to focally modulate neuronal activity. An increasing amount of studies demonstrate reduction of tinnitus after repeated sessions of low-frequency rTMS and indicate that rTMS might represent a new promising approach for the treatment of tinnitus. However available studies have been mono-centric and are characterized by small sample sizes. Therefore, this multi-center trial will test the efficacy of rTMS treatment in a large sample of chronic tinnitus patients.

**Methods/Design:**

This is a randomized, placebo-controlled, double-blind multi-center trial of two weeks 1 Hz rTMS-treatment in chronic tinnitus patients. Eligible patients will be randomized to either 2 weeks real or sham rTMS treatment. Main eligibility criteria: male or female individuals aged 18–70 years with chronic tinnitus (duration > 6 months), tinnitus-handicap-inventory-score ≥ 38, age-adjusted normal sensorineural hearing (i.e. not more than 5 dB below the 10% percentile of the appropriate age and gender group (DIN EN ISO 7029), conductive hearing loss ≤ 15dB. The primary endpoint is a change of tinnitus severity according to the tinnitus questionnaire of Goebel and Hiller (baseline vs. end of treatment period). A total of 138 patients are needed to detect a clinical relevant change of tinnitus severity (i.e. 5 points on the questionnaire of Goebel and Hiller; alpha = 0.05; 1-beta = 0.80). Assuming a drop-out rate of less than 5% until the primary endpoint, 150 patients have to be randomized to guarantee the target number of 138 evaluable patients. The study will be conducted by otorhinolaryngologists and psychiatrists of 7 university hospitals and 1 municipal hospital in Germany.

**Discussion:**

This study will provide important information about the efficacy of rTMS in the treatment of chronic tinnitus.

**Trial registration:**

Current Controlled Trials ISRCTN89848288

## Background

Subjective tinnitus is a frequent auditory sensation experienced in the absence of an external or internal acoustic stimulus. Tinnitus may present only sporadically or may manifest as constant ear-ringing of high intensity that entrains significant morbidity and may progress to a chronic debilitating condition. There is increasing evidence from electrophysiological and functional neuroimaging studies that tinnitus results from increased neuronal activity within the central auditory pathways [1]. Similar like in auditory hallucinations [2] the increased neuronal firing in the auditory cortex results in the perception of a phantom sound. This notion is supported by recent neuroimaging studies which point to a pathologically over activated, distributed cortical network involving the inferior colliculus [3], the thalamus [4], and the primary auditory cortex [4-7] in subjects with tinnitus. The pathophysiological relevance of this network has been demonstrated recently by transient suppression of tinnitus after high-frequency rTMS to the temporal and temporo-parietal cortex [8,9].

Low-frequency rTMS (1 Hz) is known to reduce neural activity in directly stimulated brain regions [10,11] as well as in structurally connected remote brain regions [11,12]. For these reasons low-frequency rTMS has been proposed as an innovative and causally orientated treatment strategy for pathological conditions with increased cortical activity [13]. Consequently, applied to the left temporo-parietal cortex rTMS has been repeatedly demonstrated to reduce auditory hallucinations in patients with schizophrenia [14].

In pilot studies, first evidence for a beneficial effect of magnetic resonance imaging (MRI) and positron emission tomography (PET) guided neuronavigated low-frequency rTMS has been found in patients with chronic tinnitus [15]. This finding has been confirmed by several controlled trials which all demonstrated a significant reduction of tinnitus severity after five to ten days of active rTMS as compared to sham stimulation [16-18]. Neurophysiological work could recently detect that rTMS-induced improvement in tinnitus complaints was paralleled by changes in cortical excitability, suggesting, that this beneficial therapeutic effect is associated with the induction of neuroplastic processes [19]. In line with these data, neuroimaging studies using voxel-based morphometry (VBM) demonstrated that low-frequency rTMS over auditory brain regions is able to induce profound changes in gray matter both in cortical auditory brain areas as well as in the thalamus [12]. Since neuroplastic alterations at the level of the thalamus seem to be essential in the generation of chronic tinnitus [20], low-frequency rTMS may represent a new approach for treating this disorder by inducing neuroplasticity in selective cortical networks closely linked to its pathogenesis. The use of rTMS in chronic tinnitus is further supported by studies showing that rTMS has beneficial effects in a variety of neuropsychiatric disorders associated with focal hyperexcitability such as focal dystonias, focal epilepsy and posttraumatic stress disorder [11,21,22].

Taken together, a multitude of studies indicate a potential of low-frequency rTMS for the treatment of auditory phantom perceptions. With regard to chronic tinnitus, especially imaging guided rTMS has been proven to be beneficial in the treatment of chronic tinnitus. Since neuronavigated rTMS is sophisticated, costly and time consuming this kind of application is strongly limited and not applicable in routine activity. Due to these considerations, a simple and reliable method for stimulating the auditory cortex based on the 10–20 EEG system has been recently developed [23] and will be used in the present trial. Furthermore, studies so far investigated only relatively small populations. Therefore, in order to render rTMS as an effective treatment according to the principle of evidence based medicine, it is necessary to assess the efficacy of this treatment in a properly designed and conducted randomized-controlled trial in a large patient sample.

## Methods

### Design of the trial

This is a multicenter, randomized, patient and observer-blind, sham-controlled, parallel-group study of 2 weeks 1 Hz rTMS treatment plus 24 weeks follow-up in patients with moderate to severe chronic tinnitus. Eligible patients will be randomly assigned to either 2 weeks real rTMS treatment or sham treatment (figure 1).

**Figure 1 F1:**
[figure not shown]
Trial design.

### Study population

Female and male subjects aged 18 to 70 years are eligible for study participation if they meet the following criteria:

#### Inclusion criteria

• Written informed consent

• Diagnosis of chronic tinnitus

• Patient has a score of ≥ 38 on the Tinnitus Handicap Inventory (assessed during routine clinical diagnostics in the last 12 weeks before start of treatment)

• Tinnitus duration of more than 6 months

• Age-adjusted normal sensorineural hearing determined by an audiogram within the last 12 weeks before start of treatment, i.e. no more than 5 dB below the 10 % percentile (DIN EN ISO 7029) of the appropriate age and gender group in all measured standard frequencies. Furthermore, no conductive hearing loss of more than 15 dB in neither of the measured standard frequencies.

• naïve regarding rTMS

#### Exclusion criteria

• Objective Tinnitus

• Other forms of tinnitus treatments at the same time

• Clinically relevant psychiatric co-morbidity as judged by an experienced psychiatrist, especially diagnose groups F1-3 according to the International Classification of diseases (ICD-10)

• Concomitant treatment with psychotropic drugs

• History or evidence of significant brain malformation or neoplasm, head injury, cerebral vascular events, neurodegenerative disorder affecting the brain or prior brain surgery

• Severe unstable somatic co-morbidity

• Cardiac pace makers, other electronic implants, intracranial metallic particles

• History of seizures or epileptic activity

• Pregnancy and lactation

• Women in child-bearing-age without contraception

• Patients who cannot communicate reliably with the investigator or who are not likely to cope with the requirements of the trial

• Participation in a clinical trial within the last 30 days before start of this clinical trial

### Participating centers

This study will be conducted by otorhinolaryngologists and psychiatrists with wide experience in the treatment of patients with chronic tinnitus from seven university hospitals and one municipal hospital all over Germany. All participating centers have experience in conducting rTMS-treatment studies.

### Study treatments

Screening is performed during the routine clinical tinnitus-consultations, and no additional study specific investigations are necessary to determine eligibility. After screening, written informed consent, baseline assessments, and randomization, patients will be treated with either real or sham low-frequency rTMS over a period of 2 weeks. rTMS will be administered according to current safety guidelines [24]. Magstim Super Rapid (The Magstim Company Ltd, Whitland, UK) or Medtronic MagPro (Medtronic GmbH & Co. KG, Düsseldorf, Germany) stimulators will be used for stimulation as available in the participating centers. Figure-of-eight-coils will be used for real stimulation. Sham stimulation will be carried out by tilting the coil 45° away from the skull with one wing touching the skull. The stimulation parameters have been chosen according to successful pilot studies [15,25] and modified with respect to duration, coil positioning and control condition. Recent data point to a dose-response relationship of rTMS treatment in a variety of neuropsychiatric diseases as well as in tinnitus treatment [23,26]. Furthermore, coil positioning using the 10–20 EEG-system has been proven to guarantee exact placement of the TMS coil over the auditory cortex without the need of using MR- and PET-guidance. Finally, finding an adequate placebo condition [27] is still under debate in clinical rTMS studies [28]. Here, sham stimulation will be performed by distortion of the magnetic coil 45° away from the skull with one wing touching the skull. In contrast to sham coils, this kind of sham stimulation does not induce a sufficiently strong magnetic field in the brain tissue to evoke any biological response but is still eliciting some kind of skull sensation. Especially in the context of tinnitus treatment studies, controlling for somatosensory stimulation seems to be critical since somatosensory input is able to modulate tinnitus sensation [1].

After screening, written informed consent, and baseline assessments, patients will be randomized to one of two parallel groups with the following stimulation parameters:

**Treatment group **will receive real stimulation: 2 × 5 sessions, 1 Hz rTMS, stimulation intensity 110% related to the individual resting motor threshold, 2000 stimuli per session, coil position 10–20 guided over left primary auditory cortex.

**Control group **will receive sham stimulation by distortion of the magnetic coil 45° away from the skull with one wing touching the skull. Coil positioning and stimulation parameters as in the treatment group.

At the beginning of the first treatment session, the individual resting motor threshold for the right abductor pollicis brevis muscle of each participant will be determined according to [29].

### Blinding

As already mentioned, blinding constitutes a substantial methodological challenge in rTMS studies. Therefore, a blinded design will be applied, in which patients and clinical raters will be blind to treatment conditions (observer blind). rTMS treatment will be provided by the non-blinded study staff. Patients have to be naïve regarding rTMS treatment and will not be informed about technical details of rTMS application. As the non-blinded study staff applying rTMS treatment needs to know whether real or sham rTMS is to be applied, and automatic rTMS is methodologically not feasible in clinical settings to date, the non-blinded study staff applying rTMS will be instructed not to communicate the treatment arm to anybody involved in patient management, in order to prevent any impact on blinding. The investigators performing all other assessments will be experienced physicians, not involved in rTMS treatment of the patient, and will perform all study specific procedures, e.g. getting informed consent, handing out clinical questionnaires or discussing any details about the conduct of the study with the patients. To assess successful blinding of the trial, each patient will be asked at the final visit (V14, day 181) whether or not he or she guesses to have been treated with real or sham rTMS.

### Objectives

#### General objective

Aim of this trial is to evaluate the efficacy of low-frequency rTMS in the treatment of chronic tinnitus. Based on the findings in pilot studies we hypothesize that two weeks treatment of low-frequency rTMS is more efficient in alleviating symptoms of chronic tinnitus and improving secondary symptoms like quality of life, cognitive functioning or depressive symptoms than sham treatment.

#### Primary objective

To evaluate the efficacy of real rTMS versus sham rTMS in the treatment of chronic tinnitus by means of a change of tinnitus severity according to the tinnitus questionnaire of Goebel & Hiller ([30], a self-rating questionnaire; baseline versus day 12).

#### Secondary objectives

To evaluate the efficacy of real rTMS versus sham rTMS

- in reducing tinnitus severity according to the tinnitus questionnaire of Goebel & Hiller and Tinnitus Handicap Inventory (THI; a self-rating questionnaire; [31]) during the follow-up period (screening versus baseline versus days 5, 12, 18, and weeks 10 and 26),

- in changes of quality of life of patients as measured by the SF 12 (a self-rating questionnaire [32]; baseline versus days 5, 12, 18, and weeks 10 and 26),

- in changes of depressive symptoms as measured by the Beck Depression Inventory (BDI; a self-rating questionnaire; [33]; baseline versus days 5, 12, 18, and weeks 10 and 26),

- in changes of psychometric parameters of tinnitus (tinnitus minimal masking level and tinnitus loudness) as assessed by audiological evaluation (screening versus day 18),

- in changes of structural and functional neuroplastic adaption processes as detected by voxel-based morphometry (VBM) and paired-pulse TMS (baseline versus day 12).

### Adjunctive measures

Further important factors that may influence treatment outcome may be clinical characteristics [34], the individual psychic resilience and personality traits. These will be assessed by using the German versions of the Tinnitus Sample Case History Questionnaire [[35]; please see also the URL in the Availability and requirments section , the NEO-FFI (a validated self-report questionnaire for measurement of the Five Factor model basic personality traits, neuroticism, extraversion, openness to experience, agreeableness, and conscientiousness; [36]) and the RS-11 (a patient self-rating to determine psychic resilience [37]).

### Enhancing quality of outcome measures

Tinnitus is a subjective sensation that cannot be measured by any objective parameter. Therefore, validated self rating scales (Tinnitus Handycap Inventory (THI) [31] and Tinnitus Questionnaire of Goebel and Hiller (TQ) [30]) are the only instruments to assess changes in tinnitus symptoms. Furthermore, tinnitus symptoms are often fluctuating and are influenced by attention. To minimize biases by spontaneous fluctuations or interactions with the trial staff, the rating scales will be handed out to the patient at the beginning of each visit *before *any other action will be taken. The patient should be seated in a quiet, comfortable room without any disturbances while answering the questionnaires. Furthermore, to increase the stability of the baseline measurement, tinnitus specific assessments (THI and TQ) will be performed three times (at the baseline visit and two times during the baseline week before the first treatment session), and the average over three measurements will be used as baseline value.

### Determination of sample size

Based upon our clinical experience, a difference of 5 points in tinnitus score (range: 0 – 80) according to the TQ is both clinically relevant and observable in a study setting [34], and 0.486 is a conservative estimate of the effect size [15,23,25,34]. Requiring a power (1-β) of 0.80 for detection of such an effect with a two-sided unpaired t-test (at a level of α = 0.05) leads to a sample size of 68 per arm (active vs. sham). A simulation study was conducted based on the pilot data, to study possible implications of incorporating center effects and baseline levels in the analysis, in which it was confirmed that the planned analysis of covariance indeed provided a power of about 0.80, given a sample size of 136. To account for the possibility of a substantially larger effect size, a scheduled interim-analysis will be carried out at the 50% recruitment level, so that a 138 subjects are needed in total (see e.g. [38]). Assuming that less than 5 percent of patients will fail to provide post-baseline data, 150 patients will be randomized to make sure that the target number of 138 evaluable patients will be reached.

### Randomization

Before the trial starts, randomization lists will be generated by the Clinical Trials Center, University Medical Center Freiburg, with a 1:1 treatment ratio, stratified by study center and with randomly varying block sizes. At each center, local investigators will have to confirm eligibility of enrolled patients and the non-blinded study staff will forward their request for randomization by fax to the randomization center, located at the department of the lead investigator. There, the randomization lists will be securely stored with none of the clinical staff involved in the trial having access to it. The randomization center will send the allocated treatment by fax to the local non-blinded staff performing rTMS. In addition, a standard email including a statement that the patient has been successfully randomized, will be send to both, the blinded and non-blinded study staff of the center as well as to the monitor.

### Statistical Analysis

The primary endpoint for evaluation of efficacy of rTMS for tinnitus is the change from baseline to day 12 in the tinnitus score (TQ total score). The treatment effect will be estimated on an intention-to-treat basis including all patients with post-baseline data (carrying forward day 5 measurements if day 12 is missing), in an analysis of covariance including treatment and average baseline score as fixed factors and center as a random factor. Interim analysis for TQ change at day 12 will be carried out on the first 76 randomized patients following an O'Brien and Fleming type sequential design with overall two-sided significance level 0.05 (0.0052 at interim, 0.0481 at final analysis; [38]). If more than 5% of patients fail to provide post-baseline data, the primary analysis will be complemented by sensitivity analyses exploring potential biases induced by patterns of missingness which will be investigated by logistic regression on comprehensive baseline information.

Secondary analyses of TQ change over time will be performed in longitudinal linear mixed models based with a pre-specified model-building strategy. For the other secondary objectives with respect to rating scales (THI, SF 12, BDI, and CGI) a similar strategy will be employed as applicable. For changes in cortical excitability and changes in psychometric parameters of tinnitus assessed by audiological examination, one-way ANOVA analysis will be used, and for changes in brain structure voxel-based morphometry (VBM) will be used.

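### The 5% trigger for missing-data sensitivity analyses counts patients with no post-baseline data, not missing day-12 endpoints, so carried-forward endpoints never count, and the protocol defines the 5% in two conflicting ways

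*Protocol article*

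**What the plan says.** Four statements in the protocol article bear on this point.

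- **Endpoint** (Statistical Analysis): "the change from baseline to day 12 in the tinnitus score (TQ total score").
- **Analysis set and missing endpoints** (same section): the analysis is called intention-to-treat, "including all patients with post-baseline data (carrying forward day 5 measurements if day 12 is missing").
- **Trigger** (same section): "If more than 5% of patients fail to provide post-baseline data, the primary analysis will be complemented by sensitivity analyses". These are described as "exploring potential biases induced by patterns of missingness which will be investigated by logistic regression on comprehensive baseline information".
- **Expected loss.** Determination of sample size has "Assuming that less than 5 percent of patients will fail to provide post-baseline data". The Abstract (Methods/Design) has "Assuming a drop-out rate of less than 5% until the primary endpoint". The Timing section gives 138 patients with post-baseline data and, in the same sentence, a loss below 5% for the primary outcome.

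**The concern.** A trigger for missing-data sensitivity analyses should respond to missingness in the endpoint it protects. This one responds to something else. A patient seen on day 5 but not on day 12 lacks the primary endpoint, yet is analysed with an earlier score and counts as having provided data. The count stays at zero however many day-12 scores are filled this way.

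At stake is whether the trial would ever test its dependence on the carried-forward values. Day 5 falls at the end of the first of two treatment weeks. If the effect is still building then, carrying day 5 forward dilutes the day-12 contrast. If substitution is more frequent in one arm, it can bias the contrast. In addition, randomised patients with no post-baseline data are left out of the primary set, and that exclusion goes unexamined until it passes 5%.

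**Working it through.** **1. The plan's own figures.** The inputs from Determination of sample size are effect size 0.486, a 5-point difference, two-sided alpha 0.05 and power 0.80. The exact two-sample t-test needs 67.43 per arm, so 68, with power 0.803 at 68. The stated 68 per arm (136 in total) is reproduced. For loss, 138 / 0.95 = 145.3, so 146 would suffice and 150 is adequate. No sample-size figure is in error. The implied SD is 5 / 0.486 = 10.29 points.

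**2. What the trigger counts.** 5% of 150 is 7.5, so more than 5% means 8 or more patients.

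| Situation among 150 randomised | Count under the written rule | Count if the rule were missing day-12 TQ |
|---|---|---|
| 7 with no post-baseline data | 7 (4.7%), no check | 7, no check |
| 8 with day 5 but no day 12 | 0, no check | 8, check |
| 30 with day 5 but no day 12 | 0, no check | 30, check |
| 60 with day 5 but no day 12 | 0, no check | 60, check |

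**3. The two definitions of the 5%.** A patient with a day-5 score only is a loss under the Abstract's wording and evaluable under that of Determination of sample size and Statistical Analysis. The Timing sentence uses both notions at once. Table 1 also schedules TQ after day 12. A patient who misses days 5 and 12 but returns later therefore has post-baseline data, does not count towards the trigger, and has no stated value for the primary analysis.

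**4. Illustration of size.** The documents give neither a day-5 effect nor an expected substitution rate, so both are assumptions. Let m be the share of day-12 scores carried forward, equal in both arms, and f the share of the 5-point effect already present at day 5.

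Expected effect = 5 × (1 − m + m × f)

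Power is for a two-sided t-test with standardised effect equal to the expected effect / 10.29. It uses 75 per arm, because all 150 patients are analysed in this scenario, and the final-analysis alpha of 0.0481.

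| m | Patients | Effect, f = 0 | Effect, f = 1 | Power, f = 0 | Power, f = 1 |
|---|---|---|---|---|---|
| 10% | 15 | 4.5 | 5.0 | 0.75 | 0.84 |
| 20% | 30 | 4.0 | 5.0 | 0.65 | 0.84 |
| 40% | 60 | 3.0 | 5.0 | 0.42 | 0.84 |

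For m = 20% and f = 0, for example: 5 × 0.80 = 4.0 points. At f = 0.5 the effect is 5 × (0.80 + 0.10) = 4.5 points and power is 0.75. The trigger count is zero in every row.

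**5. Unequal substitution.** If scores in an arm improve between day 5 and day 12, carrying day 5 forward understates that arm's improvement. More substitution in the real arm then shrinks the difference, and more in the sham arm enlarges it. The sign cannot be known in advance.

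**The case against.** The strongest reply is that few day-12 scores should be missing. The Visit schedule section keeps assessing efficacy at the outstanding visits after treatment is stopped, and it names visit 11, which is day 12. Days 5 and 12 are a week apart within a schedule of weekday visits, and the protocol expects loss below 5%. Longitudinal mixed models of TQ are also planned unconditionally as secondary analyses. All of this stands and softens the consequence. It does not repair the rule: patients who leave the study altogether can still lack day 12, and the mixed models are not named as a check on the carried-forward result.

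Several stronger readings are tempting but are not supported:

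- **The missingness model ignores treatment arm.** The text refers to "patterns of missingness which will be investigated by logistic regression on comprehensive baseline information" and does not name arm. In a condensed article that silence does not show that arm is excluded, or that the regression is the whole of the sensitivity analysis.
- **The model wrongly omits day-5 response.** Patients who count towards the trigger as written have no day-5 score. Day 5 becomes usable only once the trigger is redefined.
- **The margin of 12 patients (150 − 138, or 8%) could be lost unexamined.** Eight per cent exceeds 5% and would set off the check. The unexamined ceiling is 7.
- **A single figure for the dilution.** One could assume that benefit builds linearly over the sessions. The documents give no basis for that, so only the range is defensible, and it includes no loss at all.
- **The intention-to-treat label conceals the exclusion.** The same sentence discloses the set. Renaming it modified intention-to-treat is a matter of labelling, and a compulsory tipping-point analysis is a preference. Neither carries this point.

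**Conclusion.** The point holds as a badly fixed rule, not as a detail left to a fuller document. The article itself sets the trigger, sets it on the wrong quantity for a day-12 endpoint, and describes the same 5% differently elsewhere. Two consequences follow from the wording alone: carried-forward endpoints never count, and up to 7 of 150 randomised patients can be excluded without a check.

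The effect on the result is not known. At an assumed 20% equal substitution with all 150 analysed, it ranges from nothing (5.0 points, power 0.84) to a fall to 4.0 points and power 0.65. The 20% is illustrative, not a forecast, and a sensitivity analysis would reveal the dependence on carry-forward rather than restore power. It would be reasonable to correct this before analysis. It does not undermine the design.

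**What to change.** - Define the trigger as missing day-12 TQ among all randomised patients (8 or more of 150), or drop the condition and always run the sensitivity analysis.
- Have that analysis re-estimate the day-12 treatment effect in all randomised patients without carrying day 5 forward. A longitudinal mixed model would serve, as would multiple imputation using treatment arm and day-5 TQ where available.
- Use one definition of the 5% in the Abstract, Determination of sample size, Statistical Analysis and Timing.

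The cost is wording and a little extra analysis work. No new data are needed, since TQ is already collected at day 5, day 12 and the follow-up visits.

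### A logistic regression of missingness on broad baseline data would be overfitted if many predictors enter and cannot bound dropout bias; a fixed tipping-point analysis would serve better

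*Protocol article*

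**What the plan says.** The Statistical Analysis section of the protocol article defines the primary analysis as an ANCOVA of the TQ change from baseline to day 12, with treatment, average baseline score and center. It includes patients with some post-baseline data and carries day 5 forward where day 12 is missing. Patients with nothing after baseline are therefore not analysed.

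If more than 5% of patients are in that position, sensitivity analyses are to explore the resulting bias, based on "patterns of missingness which will be investigated by logistic regression on comprehensive baseline information". No other missing-data tool is named.

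Determination of sample size gives the expected scale of loss: "Assuming that less than 5 percent of patients will fail to provide post-baseline data, 150 patients will be randomized" to secure 138 evaluable patients.

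The baseline data are wide. Under Adjunctive measures, one instrument alone contributes five traits: "neuroticism, extraversion, openness to experience, agreeableness, and conscientiousness". The Study Plan table adds TQ, THI, BDI, SF 12, CGI, tinnitus severity, RS-11, neuropsychological testing and paired-pulse TMS.

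**The concern.** Two separate problems meet in this step.

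First, the number of missing patients is small next to the number of candidate predictors. If many enter one model, it can show an impressive pattern where none exists, or miss one that does. It would then be a poor guide to any sensitivity analysis built on it.

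Second, the bias at issue for a self-rated endpoint comes from patients who leave because of what they experience once treatment begins. A model with only baseline predictors carries no information on that, however many patients are missing. A reader of the final report would still want to know how bad the unseen outcomes would have to be before the conclusion changes. The named tool does not answer that question.

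**Working it through.** **The plan's own figures.** From Determination of sample size: "0.486 is a conservative estimate of the effect size", a 5-point TQ difference, two-sided α = 0.05 and power 0.80. The exact two-sample t-test needs 67.4, so 68 per arm, with power 0.803 at 68. This reproduces the plan. The implied SD is 5 / 0.486 = 10.29 points. The interim analysis raises the total: "so that a 138 subjects are needed in total".

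**Number of events.**
- Trigger: 0.05 × 150 = 7.5, so at least 8 missing.
- Planned allowance: 150 − 138 = 12, which is 12 / 150 = 8%.
- No upper limit is stated. The chance of 13 or more missing is 0.04, 0.42 and 0.75 at true loss rates of 5%, 8% and 10% (assumed rates).

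**Number of predictors (an assumption, since the article gives none).** Age, sex, tinnitus duration, THI, TQ, BDI, SF 12, CGI, tinnitus severity, five personality traits, RS-11, attention test, paired-pulse TMS, masking level and loudness make 19 at one variable per instrument. With treatment arm that is 20. Center, with 8 sites, would add 7 more.

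**Events per predictor** = missing patients / predictors:
- 4 predictors: 8/4 = 2 to 12/4 = 3
- 10 predictors: 0.8 to 1.2
- 20 predictors: 0.4 to 0.6

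**Simulation with no true pattern** (n = 150, continuous predictors, ordinary maximum likelihood):

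| Missing | Predictors | Complete separation | Overall test rejects (nominal 5%) | Mean apparent AUC |
|---|---|---|---|---|
| 8 | 20 | about 9–12% | about 15–19% | 0.91 |
| 12 | 20 | under 1% | about 15% | 0.85 |
| 8 | 10 | 0% | up to about 10% | 0.80 |
| 12 | 10 | 0% | within about 5–10% | 0.75 |

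About 22 missing with 20 predictors still gives rejection in about 10 to 13%.

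**Power with one predictor.** A predictor with an odds ratio of 2 per SD, fitted alone, is detected with probability 0.42 at about 8 missing, 0.58 at about 12 and 0.79 at about 21.

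**Dropout driven by outcome.** Assume that dropout in the real arm depends only on the day-12 outcome, with log-odds 1.5 per SD, independent of baseline. The test of missingness on baseline then rejects in 3.5 to 4.7% of datasets, its nominal level. Meanwhile the completers' treatment difference shifts by about 1.0 to 1.3 TQ points at roughly 8 to 12 missing, and by 2.1 points at about 22. Against the 5-point target the first range is 20 to 26%.

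**A direct bound.** Shift in the arm difference = (missing in arm / patients in arm) × δ.
- 6 missing of 75, δ = 10: 6/75 × 10 = 0.8 points, or 0.8/5 = 16% of the target.
- All 12 of the allowance in one arm, δ = 10: 12/75 × 10 = 1.6 points, or 32%.
- Standard error of the difference at 69 per arm, without covariate adjustment: 10.29 × √(2/69) = 1.75. So 0.8 points is 0.8/1.75 = 0.46 of a standard error, enough to matter near the threshold.

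**The case against.** The strongest reply is that the article does not commit to one large unpenalised model. It gives no predictor list, count or fitting method, and such detail commonly sits in a full protocol or SAP that is not shown. Screening variables singly, a reduced model or a penalised fit would all match its wording. This stands. The overfitting figures hold only if many predictors enter jointly, and the absence of a list is not itself a fault.

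Three stronger readings are tempting, and the documents do not support them.
- A reader might infer that at most about a dozen patients can be missing. Twelve is the planned buffer. The trigger has no ceiling, and the step matters most when losses exceed the plan.
- A reader might infer that the regression cannot be fitted. With 3 to 10 predictors the simulations show no separation and rejection of roughly 5 to 10%. Low power then reflects the few missing patients, and a penalised fit would not cure that.
- A reader might infer that the regression is offered as a test for outcome-dependent dropout. The article presents it as a description of patterns that supports separate sensitivity analyses. No method can confirm such dropout from observed data, and a delta analysis only measures its consequence under stated assumptions.

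The step is also conditional and supplementary. The visit schedule limits losses by asking for efficacy assessments at all outstanding visits after treatment discontinuation, and for a termination visit where possible.

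What remains is that the one tool named points toward a broad baseline set, and that no baseline-only model can say how far the excluded patients could move the result.

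**Conclusion.** The point holds in a limited form. Within the planned allowance of 8 to 12 missing of 150, a joint logistic regression on broad baseline data would be overfitted and low-powered if many predictors enter. About 20 predictors is an assumption, and with 10 or fewer the distortion is modest. The second limb needs no such assumption: missingness modelled on baseline alone cannot quantify bias from dropout driven by later experience, and the patients concerned are outside the primary analysis.

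The size is moderate: 0.8 points for 6 of 75 missing and a 10-point shift, and about 1.0 to 1.3 points under the assumed outcome-driven dropout. Neither overturns a clear 5-point effect, but either could decide a result close to 0.0481. This is a worthwhile low-cost improvement and does not show that the primary analysis is wrong.

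**What to change.** 1. Restrict the description of missingness to a few pre-named variables, namely treatment arm and average baseline TQ. If a model is wanted, use a penalised (Firth) logistic regression.
2. State one concrete sensitivity analysis of the primary ANCOVA. Multiply impute day-12 TQ for patients with no post-baseline data from arm, average baseline TQ and center. They have no day-5 value, so day 5 cannot serve as a predictor for them. Worsen the imputed real-arm values in fixed steps from 0 to 10 points (0 to 2 times the 5-point target). Report the shift at which the result crosses 0.0481.
3. Leave the day-5 carry-forward rule as it is for this purpose. Those patients are already in the primary analysis.

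Cost: one paragraph in the analysis section and a little more programming, with no new data. The downside is that the delta range must be chosen and defended in advance.
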